#### 6.7.1 Costs

Subjects will not incur any costs for their study participation.

#### 6.7.2 Compensation

Each practice will receive $2000 for their participation in the study, to be provided once they complete intervention implementation and have contributed the requisite number of semi-structured interviews and surveys for the study. This is meant to defray the cost of clinician and staff time for participating in assessments and trainings, and for the practice champion’s time to coordinate with the research team.

Subjects will receive $25 for participating in semi-structured interviews. Clinicians will not be compensated separately for surveys.

## 7 STUDY INTERVENTION(S) OR EXPERIMENTAL MANIPULATION(S)

### 7.1 Study Interventions(s) or Experimental Manipulations(s) Administration

#### 7.1.1 Study Intervention or Experimental Manipulation Description

***Conceptual Framework.*** The practice redesign tools and approaches of the PT-AWV intervention are based on principles consistent with the Practice Change and Development Model,[^159^](#_ENREF_159)^,^[^160^](#_ENREF_160) which attempts to transform culture and thinking to yield sustained changes in practice. The model has 4 major interdependent elements. Initial assessments with practices will yield information about the different elements of the model so that intervention strategies can be customized to practices’ unique characteristics, including staff workflow, resources, and EHR capability. The intervention has two major components. It combines the use of electronic health record (EHR) generated tools with practice redesign tools and approaches (**Table 3)**.

***EHR-based tools.*** EHR-based tools will be provided to practices (or “turned on”) at the beginning of the intervention implementation period and will be available for the duration of the study. UCLA and the DARTNet Institute will work with organizations and practices to modify and/or provide EHR-based tools, based on organizational/practice needs. The UCLA investigative team will work with UCLA population health team to make modifications in UCLA Health’s Epic EHR to provide capabilities below selected by the health system.

The EHR-based tools draw from EHR data to generate a patient registry that describes fulfillment of AWVs and recommended preventive health services. Practices can use registries for patient outreach at the point-of-care, or for prompting patients to schedule appointments for AWVs through contact by telephone, letters, text messages or patient portals. Tools that draw on the registries have features that can be customized based on practice staffing and preferred workflows. These include:

- Point-of-care reports to office staff, clinicians, and patients detailing services (e.g., AWVs, preventive health services) that are at goal, that are not at goal, or not performed.
- Tracking of patient completion of recommended AWVs and preventive health services, for example through a web-based dashboard.
- Patient notifications about the need for an AWV and/or preventive health services. Notifications and information tailored to patient race/ethnicity can be provided at the point-of-care as a personalized prevention plan (one of the requirements of an AWV), and through a letter or phone, email, or text-messaged reminders (to patients who agree to receive messages from the practice).
- Reminders for patients who do not complete clinician-ordered preventive services within a specified timeframe of the order (adjusted for local scheduling limitations) that can be sent via phone, email, or text messaging.

***Practice redesign tools and approaches*** involve designing workflows to help practices use EHR tools and training members in the practice on using the workflows and on completing assigned tasks when patients arrive for an AWV. Training sessions will be performed via a video-conferencing platform. Resources include templates for required AWV components such health risk assessments and patient personalized prevention plans, patient messaging about AWVs, clinician documentation templates, and patient-targeted educational materials about the need for different preventive health services. There will be a focus on materials tailored to racial/ethnic minority patients and in non-English languages (drawn from existing materials found on the internet from expert organizations and the scientific literature). Resources also include sample workflows, including those developed by other practices. There also may be an option to notify patients who fail to complete recommended services, with the method of communication tailored to patient preferences. Feedback reports on rates of completion of AWVs and preventive health services, coupled with recommendations for continued improvements, will be provided monthly or quarterly (based on practice preference).

With an eye toward future broad dissemination of the intervention, we will modify our original intervention by posting all resources on a **study website** so that participating practices and patients can browse, select and download relevant templates and materials. Video recordings of clinician and staff training sessions will be available. As we learn more about what works in different practice settings and how people orient to the website, we will refine and update available materials, add to sample practice workflows, and modify instructions for using the website. Our larger goal is for the website to stand alone as a starting point for practices to access on their own, without requiring guidance from outside investigators.

**Tailoring of PT-AWV intervention components for practices**. Implementation of the PT-AWV intervention (the intervention) will take place at the practice level over 6 months.

The exact content of the intervention will be tailored based on each practice’s individual needs. For example, one practice may ask staff to use the AWV patient registry to invite patients to schedule a future AWV, while another practice may use the registry at the point-of-care to add an AWV to a visit scheduled on that day (if a clinician has availability). Similarly, practices will customize their selection of practice redesign tools and approaches and will work with the investigative team to tailor their workflows to match their individual resources and capabilities. **Table 3** describes examples of options for intervention tailoring.

| **Table 3. Major Intervention Tools and Approaches and Options for Tailoring *** | |
| --- | --- |
| **Tools / Approaches to address identified barriers to AWV use** | **Examples of Options for Tailoring** |
| **EHR-based tools** (implementation of tools depends on EHR capabilities and potential for modification) | |
| Patient registry to identify those without an AWV in the past 12 months and that includes information on preventive health services use | - Registry can be embedded in EHR or presented as a separate electronic “dashboard” - Practices may choose to receive EHR notifications |
| Point-of-care information regarding AWV and preventive service completion | - Practices select to receive point-of-care information electronically (e.g., in EHR, through dashboard) or on paper |
| Individualized patient preventive health plans | - Practices can select delivery format (paper, electronic) of preventive health plans |
| Message patients about need for services | - Practices can select timing and delivery method (EHR patient portal, postal mail, text message) of patient messages and reminders |
| Patient reminders if ordered services not completed |  |
| **Practice redesign tools and approaches** | |
| **Workflows (developed iteratively based on practice preferences and feedback)** | |
| For using EHR-based patient registry | Practices develop desired workflows for using patient registry to invite and schedule patients for AWVs  - may invite patients for AWVs by phone, text message, or via patient EHR portal |
| For recommending / scheduling patients for AWVs when patients present in-person | Practices choose who should recommend / schedule patients for AWVs when they present for other types of office visits |
| For accommodating AWVs in clinician schedules | - Practices decide type of clinician(s) who will conduct AWVs (physician, physician assistant, nurse practitioner, other) - Practices determine whether they will add AWVs to existing follow-up visits for other issues - Practices decide whether AWVs will be conducted in-person versus by telehealth - Practices choose amount of time allocated for AWVs |
| For performing tasks associated with AWVs | - Practices choose how much time before AWV to ask patients to arrive - Practices define strategies to complete time-consuming required health risk assessment. Approaches include: - Send form to patients via email, postal mail, EHR portal - Staff to complete by phone - Complete in office (practices opt to complete on paper, iPad or phone, verbally; who should complete with patient) |
| For performing assessments such as for fall risk, dementia screening (instruments and trainings for select tasks are available) | - Practices can choose who will perform assessments, what instruments to use; whether to offer training for staff on selected instruments |
| **Templates for documentation, collection, and delivery of Medicare-required information for AWVs** (practices/clinicians may elect to use only selected elements of templates) | |
| Health risk assessment templates (includes question bank) | - Practices can choose which questions they want to ask - Can include assessment of social determinants of health |
| Documentation templates that include required components of AWVs | - Clinicians tailor content of their templates based on personal preferences |
| EHR data collection package (e.g., SmartSet for Epic EHR) | - Practices can modify content of EHR data collection package and order of components |
| Preventive health summary templates | - Practices may choose content and formatting of preventive health summaries from existing examples or modify based on practice/clinician/patient preferences |
| **Clinician and staff training sessions** | |
| Clinician and staff PowerPoint presentations (contain information on benefits of AWVs, terminology, billing strategies, visit requirements, presentation of practice-developed workflow and role-specific tasks) | - Practices select number of training sessions, duration, participants (e.g., clinician, staff, combined) - Training sessions can be group, individual, or both - Information presented tailored based on clinician / practice motivation to provide care |
| **Other tools** | |
| ***Clinician-targeted*** |  |
| Opportunity to use data to fulfill AAFP  Maintenance of Certification practice  improvement activity | - Clinicians can choose data/metric they want to use to fulfill practice improvement activity |
| FAQs about AWVs (for clinicians) | - Practices can select frequency and modes (e.g., email, text messaging) chosen for dissemination of written materials |
| Summary of elements of IPPE and AWVs |  |
| Clinician billing tips |  |
| ***Patient-targeted*** |  |
| Messaging for contacting / informing  patients about importance of AWVs (from  AAFP) | - Practices can choose whether / how / when to send patients information - Practices may choose to make patient-facing materials available in waiting room, have office staff or clinician hand to patient during visits, mail to those on registry - Information provided to patients about preventive health screenings can be tailored by patient race/ethnicity |
| FAQs about AWVs (for patients) |  |
| Educational materials on common cancer  screenings, vaccinations (pulled from  existing sources such as the CDC) |  |
| **Feedback reports on rates of AWV and preventive health services completion**** | |
| Practice-level reports | - Practices may elect to receive reports monthly or quarterly - Practices may choose different metrics to review |
| Clinician-level reports | - Reports may compare clinicians to other clinicians in their practice (either de-identified or identifiable), or to others in the study |
| * Practices choose which tools they want to use and how they want to tailor each selected tool; selection and tailoring is based on individual practice needs and existing resources; practices are not required to use any specific tools | |

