## 4 OBJECTIVES AND ENDPOINTS

| OBJECTIVES | ENDPOINTS | JUSTIFICATION FOR ENDPOINTS |
| --- | --- | --- |
| Primary |  |  |
| Evaluate the effect of ***the intervention*** (PT-AWV intervention) on:   1. AWV utilization 2. USPSTF and CDC/ACIP-recommended preventive services | **Primary endpoints:**  **AWV utilization** will be assessed by examining: the % of eligible patients completing an AWV (CPT codes G0438, G0439, G0468) or Initial Preventive Physical Examination (IPPE) (CPT code G0422) in the past 12 months.  **Completion of recommended preventive health services** will be measured using a composite preventive health services score (% of total recommended preventive health services that are up to date (of a maximum of 12 recommended services per patient)); measured on the patient-level  **Secondary endpoint:**  **Utilization of individual preventive health services**: % of patients up to date for each preventive health service listed in **Table 2** below. | These endpoints are the primary endpoints of interest.  AWVs mediate fulfillment of clinical endpoints on preventive health services.  Completion of recommended preventive health services can improve population health and reduce mortality. |
| Secondary |  |  |
| Evaluate the effect of ***the intervention*** (PT-AWV intervention) on reducing racial/ethnic disparities in AWV utilization. | As for the primary objective, **AWV utilization** will be assessed by examining: the % of eligible patients completing an AWV (CPT codes G0438, G0439, G0468) or Initial Preventive Physical Examination (IPPE) (CPT code G0422) in the past 12 months. | Secondary endpoints will demonstrate additional effects of the intervention and provide additional information to support the importance of the primary endpoints of AWV and preventive health service utilization |
| Tertiary/Exploratory |  |  |
| Tertiary: Evaluate factors affecting implementation and sustainability of the PT-AWV intervention tools and approaches, implementation strategies, and intervention effect in diverse practice settings. | Facilitators and barriers to intervention adoption and implementation (from semi-structured interviews [with patients, clinicians and staff] and clinician surveys) | These endpoints may suggest further hypotheses for later research and will provide information about causal mechanisms regarding uptake of AWVs |

| **Table 2. Preventive health services, recommended frequency and age, and evidence for use/no use*** | | | |

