#### 7.1.2 Administration

**Initial practice assessments*.*** Initial practice assessments will be conducted prior to intervention implementation. An ***on-site practice champion*** identified by the practice will work with the investigative team to champion the intervention and its continued implementation and use, and ensure completion of all study assessments. The practice champion may be a physician, pharmacist, office manager, nurse, or other personnel.

Practice assessments will typically involve 2-3 meetings of about 30-60 minutes each, during which the investigative team will gather information regarding the practice’s motivation, resources, facilitators to conducting AWVs, current practice workflows and templates for AWVs, preferred workflows, and opportunities for change. Assessments will be performed via Zoom video conferencing, which have proven effective and efficient for intervention implementation and data collection across multiple sites,[^161^](#_ENREF_161) and enhances the potential for future widespread intervention dissemination. The study team will use information from the assessments to develop a prototype workflow, which they will present to the practice for discussion and revision. The investigators will also assess practice interest in using the resources available for download on the study website, introduce the website, and provide practices with the materials desired, as well as the website link so that they can browse, download, and use other desired resources. Discussions also will focus on selecting and tailoring EHR-based tools for their practice.

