**Intervention implementation*.*** Once initial practice assessments have been completed, the practices have developed a workflow for conducting AWVs, and have selected their desired tools, the intervention will be implemented over 6 months. Intervention implementation will consist of “turning on” selected EHR-based tools, providing access to selected documentation and other templates, and training practice members on the use of these tools. Practice training sessions will occur during this period on the established practice-specific AWV workflow, benefits of AWVs, documentation requirements, services that clinicians can perform with the AWV without incurring extra patient costs, and potential billing strategies. The research team will interface with the practice champion regularly (on average likely about once every 1-2 months based on our experiences with our pilot practices) during the 6-month implementation period to identify and remedy barriers to implementation.

The investigative team will collate information from all sites on strategies for increasing AWVs and overcoming barriers to conducting AWVs and will share pertinent insights in a quarterly newsletter for practices that have already started intervention implementation. Practices will receive feedback reports on their AWV and preventive health services completion rates starting about 4-6 months after they begin intervention implementation until 12 months post-implementation. Practices will determine the desired frequency of these reports, which can be provided monthly to quarterly.

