| Advance Care Planning | Aged 66 and older | % of patients aged 66 and older with documentation of advance care planning | soc_adv_directive | N/A |
| Hepatitis C | Aged 18-79 years of age | % of patients who received one-time hepatitis C screening | lab_hepatitis_c_ab  lab_hepatitis_c_rna  lab_hepatitis_c_genotype  lab_hepatitis_c_screen | dx_hepatitis_c  dx_hepatitis_c_acute  dx_cirrhosis  dx_hepat_carcinoma  dx_decomp_cirrhosis  dx_esophageal_var  dx_hepatic_encep  dx_ascites  doc_hospice  dx_palliative |
| Depression | 1) Entire cohort    2) Those in cohort 1 with positive finding for depression in the past 12 months  dx_depression  dx_depression_major  doc_phq9_gt9 | 1) % of patients who were screened for depression in the past 12 months  2) For those screening positive for depression, % that received follow-up care within 30 days of a positive screen | doc_depression_score  doc_depression_screen  doc_depression_screen_maternal  doc_phq2_score  doc_phq2_screen  doc_phq9_score  doc_phq9_screen  doc_depression_plan  med_antidepressant  med_antidepressant_monotherapy  ref_mental_hlth_psych  ref_behavioral_health_clinic  visit_behavioral_health  ibh_med_antidepressant | dx_bipolar_disorder  *Depression that starts during past 12 months*  dx_depression  dx_depression_major  dx_mental_beh_dis  doc_hospice  dx_palliative |
| Alcohol use | 1) Entire cohort  2) Those in cohort 1 with positive finding for unhealthy alcohol use  soc_alcohol_use_disorder  dx_alcohol_related_disorders  doc_audit_score | 1) % of patients who were screened for alcohol use one or more times within the past 24 months  2) % of patients in Cohort 1 who  screened positive and received an intervention on or up to 60 days after the date of the first positive screen (61 days total) | doc_audit_screen  doc_audit_score  soc_alcohol_screen  soc_alcohol_use_current  soc_alcohol_use_former  soc_alcohol_use_disorder  soc_alcohol_use_none  med_antialcohol  soc_alcohol_counsel_plan  soc_substance_abuse_counsel  ref_alcohol_rehab  ref_drug_addiction_mgmt  ibh_med_antialcohol | soc_alcohol_use_disorder  dx_alcohol_related_disorders  dx_dementia  doc_hospice  dx_palliative  *Exclusion only for cohort 2*  soc_alcohol_use_none |

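### About four of the composite's services are scored from chart entries that the intervention helps practices record, and nothing in the primary analysis separates recording from delivery

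*Protocol*

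**What the plan says.** **The intervention.** Section 7.1.1, Table 3, lists among the tools "Documentation templates that include required components of AWVs", health risk assessment templates and an EHR data collection package such as an Epic SmartSet. Under section 7.1.2, implementation includes "providing access to selected documentation and other templates", with training on documentation requirements. Section 5.3 sets the minimum exposure as a practice-specific workflow plus clinician training that covers AWV documentation. The tools are a menu: the Table 3 footnote says that "practices are not required to use any specific tools". The assessment before implementation (section 7.1.2) gathers information on "current practice workflows and templates for AWVs".

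**The endpoint.** Sections 5.1 and 9.2 take the primary and secondary outcomes from EHR extraction. The composite is the percentage of recommended services that are up to date, with at most 12 per patient (section 4). The Appendix (section 13) scores advance care planning from one field, `soc_adv_directive`, as the percentage "of patients aged 66 and older with documentation of advance care planning". Depression is the percentage "of patients who were screened for depression in the past 12 months", counted mainly from `doc_*` entries. Alcohol and tobacco screening draw on `doc_*` and `soc_*` entries, including status entries such as `soc_alcohol_use_none` and `soc_non_smoker`. Section 4 justifies the endpoint thus: "Completion of recommended preventive health services can improve population health and reduce mortality".

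**The analysis.** Section 10.4.2 models the composite as a whole. Its sensitivity analyses concern the shape of the time trend and the time-treatment interaction. Section 10.4.3 models each service separately as a secondary endpoint. Quality control in section 11.7 looks for out-of-range or anomalous values.

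**The concern.** The intervention can change how completely some services are recorded, and that change would follow the randomised crossover. Randomising the order of practices and adjusting for calendar time remove secular trends. They do not remove a shift in ascertainment that starts with treatment. For services evidenced by a laboratory result, a procedure or an immunization record, this matters less. For the four services scored from chart entries, a screen or discussion that took place but was not entered in a counted field does not score before crossover, and may score afterwards.

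At stake is the interpretation of the second primary endpoint. The protocol presents the composite as completion of services that benefit health. A rise that came partly from recording would still be an effect of the intervention, but not the effect claimed.

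**Working it through.** **1. The plan's own figure.** Section 10.2 and Table 4 give more than 99% power for a 10% increase in the composite. I read 10% as percentage points, which fits the disparity calculation in the same section (15% minus 10% gives the 5% reduction). I used a closed-form stepped-wedge model with 24 practices, 4 steps, 5 periods, period effects and two-sided alpha 0.05. The inputs were 800 patients per practice and ICC 0.03 and 0.05. The protocol gives no SD for the composite, so 0.17 and 0.25 were assumed; the first is about √(0.4 × 0.6 / 8). Power is about 1.00, so the stated figure reproduces.

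**2. How many documentation-scored items are in the composite?** The protocol does not list the 12 services. By the Appendix age bands, the largest set of recommended services is that of a woman aged 66 to 74:
- 4 vaccines (influenza, tetanus, zoster, pneumococcal)
- 4 tests or procedures (colorectal, mammogram, bone density, hepatitis C)
- 4 documentation-scored items (depression, alcohol, tobacco, advance care planning)

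The total is 4 + 4 + 4 = 12, so the stated maximum is reached only with all four. By the Table 2 ages, a woman aged 65 also qualifies for a Pap smear. That gives 9 services without the four, so 12 needs at least three of them. Hence k = 4, or possibly 3.

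**3. Size of a recording shift.** Let g be the rise, in points, in recorded completion of each of the k items, with no change in care, and let n be the number of eligible services. Then:

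change in composite = (k / n) × g

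Section 10.2 assumes more than 8 services per patient and section 4 caps them at 12, so n runs from 8 to 12.

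| k | g (assumed) | n = 8 | n = 12 |
|---|---|---|---|
| 4 | 10 | 4 × 10 / 8 = 5.0 | 4 × 10 / 12 = 3.3 |
| 4 | 20 | 10.0 | 6.7 |
| 4 | 30 | 15.0 | 10.0 |

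The rise needed for the whole 10-point meaningful effect is g = 10n / k. For k = 4 this is 20 points (n = 8) to 30 points (n = 12). For k = 3 it is 27 to 40 points.

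**4. Would a small shift be declared significant?** I used the model of step 1 with zero real effect, SD 0.17 to 0.25, ICC 0.03 to 0.05 and cluster autocorrelation 0.8 to 1.0. A 3.3-point shift is significant with probability 0.97 to 1.00, and a 2-point shift with probability 0.64 to 1.00. The precision that gives more than 99% power also makes a modest recording shift detectable as an effect.

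**The case against.** **The services are already modelled one by one.** Section 10.4.3 applies the same kind of model to each service, with monthly run charts. If only the four documentation-scored items moved, that would be visible. This largely stands, and a reader should not infer that the plan lacks any analysis that could reveal the problem. What is missing is a link: the protocol does not say that the primary composite will be read in the light of those results.

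**The tools are optional and not exclusive to the intervention condition.** This stands. A reader might infer that templates are installed in every practice, and only after crossover. The documents do not support that: no tool is required, and practices may already have templates. Training on AWV documentation is, however, part of the minimum exposure. That the supplied templates fill the exact counted fields is a reasonable inference, not something the protocol states.

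**The record is often the service.** A stored PHQ-9 or AUDIT score is good evidence that screening took place. Smoking and alcohol status are ordinary social-history entries with a 24-month look-back. This stands in part, and advance care planning is the clearest documentation-only item. Some of any rise would be real screening delivered at AWVs; the pooled composite cannot say how much.

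**The gains are assumed.** No baseline recording rate is given. If recording improved only among added AWV attendees, and AWV use rose by the planned 10 points, the population gain would be at most 10 points, or 3.3 to 5 composite points. Larger gains need uptake on the scale of the pilot or better recording among existing attendees. This stands.

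**Late entry of older services.** A reader might also infer that AWVs turn past vaccinations or screenings into new successes. The protocol does not say so, and the Appendix defines most items by when the service was received or performed.

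**Conclusion.** The point holds in a limited form. The composite is counted partly from chart entries whose completeness the intervention may improve, and the plan does not say how a rise confined to those entries would be read. An assumed 10-point recording gain with no change in care is worth 3.3 to 5 composite points, one third to one half of the meaningful effect. It would probably be statistically significant.

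A stronger reading, that a positive composite could be wholly a recording artefact, is not shown. It needs a gain of 20 to 30 points in all four items across the practice population with no added care, and the documents neither give nor imply such a gain. The figures rest on three or four of these items being in the composite, 8 to 12 eligible services and the assumed SDs. The AWV endpoint is counted from billing codes and is not affected in this way.

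**What to change.** In section 10.4.2:

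1. Pre-specify a sensitivity analysis, with the same model as the primary analysis, of two sub-scores: the composite restricted to services evidenced by a test result, procedure or immunization record, and the composite of documentation-scored items. Name the items in each.
2. State that a rise confined to the documentation-scored items will be reported as possibly reflecting improved recording. The primary endpoint itself need not change, and success need not be made conditional on the first sub-score.
3. Confirm that monthly up-to-date status is derived from the date of service, by the same rule in control and intervention months. This guards against late entry of older vaccines and procedures. It does not help the documentation-scored items, which is why the split is also needed.

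The cost is one or two extra models on fields already listed in the Appendix, and possibly a more cautious conclusion about the composite. No new data are required.
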